### Appraisal of intervention.

#### Data collection.

Participants will complete baseline, 3, 6, and 9 months post-intervention surveys. Trained GBMSM+NURSE partners who collected surveys in our previous studies will conduct the surveys^34,73,74,81,98^. **For YGBMSM**, the data collection location will be at the designated sites (e.g., office of community partners) determined as safe for YGBMSM in Ghana due to their extensive experience working with GBMSM on the grounds in Ghana. **For HCFs**, the data collectors will visit the facilities led by the team leader at the facility to hand over the surveys to providers, who will self-complete them at their convenience. **For PrEP and ART** adherence **biomarkers**, the HCF will provide them with consent from participants during routine check-up visits.

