### Preliminary Studies.

#### ISD experience among GBMSM and YGBMSM.

In our recent studies in Ghana^34,81^, we identified that GBMSM face various forms (e.g., experienced, anticipated, perceived, and internalized) of ISDs concerning sexual behavior or sexuality and gender expression **among their peers and healthcare workers (HCWs)**. HIV-related ISD continues to thrive due to the perception that contracting HIV signifies a punishment for sin and insufficient knowledge of HIV transmission. As such, GBMSM face insults, gossip, avoidance, and sometimes physical violence **from peers, the community, and HCWs**. In 2022, we found that over 70% of HCWs consider GBMSM mentally ill and non-Ghanaian. About 35% also said their co-workers/themselves were hesitant to care for GBMSM^81^. To circumvent ISD, many GBMSM **in slums prefer to travel outside or self-treat** as they avoid interacting HCWs, thus a need to combat ISD and increase HPART uptake. We consistently found similar results in several studies^13,34,62,64,73,74,81–89^.

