### STEP 8 (Testing/Aim 2): Test the preliminary efficacy of the intervention to address ISD and increase HPART adherence using CRT Design

We will pilot-test the *LAFIYA* multilevel intervention using a clustered randomized control trial (CRT) with 9 months of waitlist control. Our ultimate aim is to adapt the intervention and preliminary test it for future full-efficacy CRT ^118,119^. Although RCT is primarily used in HIV and behavioral interventions, we find CRT better due to our place-based focus and possible sample contamination. In our previous single arm-pilot (2P30MH062294 −20 // Yale #18–001890, PI, [name]), we identified group sleeping arrangements, observed close-knit networks of GBMSM, and the communal nature of slums as contaminants. We will create two pairs of facilities matched by size and location in each city and randomly assign them to receive the LAFIYA-HCF intervention or the control group. Based on friendship networks, we will create GBMSM groups of 5 to 8 members and randomly assign YGBMSM groups to the LAFIYA-YGBMSM intervention or control group. YGBMSM in the intervention group will be matched with intervention HCF for status-neutral services. The YGBMSM in the waitlist control group will be matched with HCFs in the waitlist control for regular testing, PrEP, and care services. Nurses from the intervention HCF will participate as guest facilitators in one of the LAFIYA-GBMSM sessions. They will use that opportunity to contact YGBMSM to visit their facility for status-neutral care. We will collect 3, 6, and 9 months post-intervention data to measure the preliminary efficacy of the intervention and then implement the intervention in the waitlist group after the completion of data collection. We will use 9 months instead of 6 to allow ample time to measure multiple components, **such as viral suppression,** over a sufficient time. **Our primary hypothesis** is that LAFIYA will increase adherence to HPART among YGBMSM participants. **Our secondary hypothesis** is that the multilevel intervention will reduce the ISD that HCF staff convey and YGBMSM experience in HCFs. It will build the HCF’s capacity to implement status neutrality. We will then **conduct a follow-up qualitative study** (FGDs and IDIs) post-intervention among implementers and participants to evaluate their experiences with the intervention and to seek a more profound understanding or explanations for some of the survey findings.

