### Measures.

#### Demography, HIV testing, and ISD descriptive variables.

We will assess important baseline characteristics for describing the sample, including age, income, gender, education, ethnicity, relationship status, religion, sexual orientation, sexual behavior, HIV knowledge, HIV testing, PrEP and ART readiness, and history. Experiences of ISDs, access, and utilization of health and social services, civic engagement, and neighborhood. **Primary outcomes:** At baseline, 3, 6, and 9 months, we will measure the preliminary efficacy of LAFIYA. We will measure knowledge of HIV and HPART; and willingness to adhere to HPART pre and post-intervention. HPART adherence characteristics (rates, time, mode, location) and biomarkers (Table 2). **Secondary outcomes:** For ISD reduction, we will measure internalized and interpersonal level ISD at baseline and post-intervention surveys among YGBMSM. We will measure HCF-level ISD to understand participant experiences at baseline and changes in HCW stigmatizing beliefs and practices (Table 2). **Implementation outcomes:** We will measure acceptability, appropriateness, and feasibility using expanded Proctors validated measures at pre-immediate and post-intervention surveys at all levels (Table 2)^103^.

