#### Data analysis.

We will use the intent-to-treat (ITT) technique to analyze data. We considered other methods (e.g., per protocol approach), but ITT is less biased since all participants are assessed whether they received the intervention or not. Data collected will be exported to Stata for cleaning and further analysis. Using the Monte Carlo Markov Chain approach based on a multivariate normal distribution of items, we will assess missing patterns in the instrument and impute missing responses with at least 70% of responses. Instruments scores will be calculated with observed and imputed responses. We will summarize the characteristics of participants and calculate Cronbach’s alpha to check internal reliability within scales. We will calculate a mean with a confidence interval for the variables and proportions of responses to the primary and secondary outcome variables. Variables with skewed distribution will be considered for being log-transformed or categorized in ordinal form. We will run inferential statistics such as paired t-test to compare pre-and post-means, McNamara’s test to compare pre-and post-proportions, and correlation analysis to examine the relationship between variables. We will also develop longitudinal models of the outcomes repeatedly measured at baseline, 3, 6, and 9 months post-intervention using a generalized linear mixed effect model (GLMM) with random intercept and peer group, which incorporate ICCs. The GLMM will include time-group interaction to estimate the intervention effect and pre-post changes. The GLMM will consist of all completed observations and drop-outs observed at least once post-intervention. Thus, we will not miss any individuals unless they are entirely missing at all post-intervention periods. Residuals will be assessed for normality assumption and influential outliers diagnosed with leverage, Cook’s distance, and DFFIT. The GLMM will be replaced with logistic and Poisson regressions with random effects when an outcome is binary and count data. We will repeat the same models separately for each site and compare the effect sizes between the sites. When we find any demographics, which are not equivalent between the two interventions, they will be included in the model as covariates. Acceptability, feasibility, and appropriateness will be evaluated with descriptive statistics of the implementation outcomes. **The process defined in AIM**1 will be used to analyze the follow-up qualitative data.

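### PrEP and ART biomarkers come only from routine facility visits, which the intervention is built to increase, so an arm comparison of observed biomarkers is a comparison of attenders and not intention-to-treat

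*Protocol article*

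**What the plan says.** - **Source of the biomarkers.** In Appraisal of intervention, Data collection, the one route stated for PrEP and ART biomarkers is that "the HCF will provide them with consent from participants during routine check-up visits".
- **Source of the surveys.** The same section schedules surveys at baseline, 3, 6 and 9 months, and for YGBMSM "the data collection location will be at the designated sites (e.g., office of community partners) determined as safe for YGBMSM".
- **Standing of the biomarkers.** Measures lists knowledge and willingness to adhere under the primary outcomes, together with "HPART adherence characteristics (rates, time, mode, location) and biomarkers (Table 2" (that table is not in the text available). STEP 8 (Testing/Aim 2) names viral suppression as a reason to follow participants for 9 months and not 6.
- **Link between arm and facility.** STEP 8 states that "YGBMSM in the intervention group will be matched with intervention HCF for status-neutral services". For the other arm it states that "The YGBMSM in the waitlist control group will be matched with HCFs in the waitlist control for regular testing, PrEP, and care services". At one session, nursing staff of the intervention facilities act as guest facilitators: "They will use that opportunity to contact YGBMSM to visit their facility for status-neutral care".
- **Expected attendance.** No rate is given. Preliminary Studies reports that many GBMSM in slums go elsewhere or treat themselves, "as they avoid interacting HCWs".
- **Analysis.** The Aim 2 Data analysis section chooses ITT because "ITT is less biased since all participants are assessed whether they received the intervention or not". The GLMM uses participants with at least one post-intervention observation. The imputation described covers missing questionnaire responses.

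**The concern.** The surveys and the biomarkers are ascertained in different ways. The surveys are scheduled for every YGBMSM participant at sites outside the health facilities. A biomarker exists only if the participant attends a facility for a routine check-up and consents to its release. Attendance happens after randomisation, and the intervention acts on it directly: its nurses invite participants in, and its facilities are trained to reduce the stigma that the protocol blames for avoidance. Controls are offered regular services.

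If biomarker availability differs by arm, a model fitted to observed biomarkers compares two self-selected groups. Randomisation does not protect that comparison, and the reason given for choosing ITT, that everyone is assessed, is not met for this component. At stake is a misleading biomarker signal, in either direction, in a pilot whose stated purpose is to inform a full efficacy trial.

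**Working it through.** **1. The plan's own figure.** Power section: 120 per arm, friend groups of 8, ICC 0.04, effect size 0.50, 5% level (two-sided assumed).

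- Design effect = 1 + (8 − 1) × 0.04 = 1.28. Effective n per arm = 120 / 1.28 = 93.75.
- Power = Φ(0.50 × √(93.75 / 2) − 1.96) = 92.8%, against 92.7% stated.
- With 108 per arm: 108 / 1.28 = 84.4, power 90.1%, against 90% stated.

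Both reproduce. They concern a measurement scale (HIV-ASES) with 10% attrition, and they do not cover an outcome observed only in attenders.

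**2. What selection can do.** The protocol gives no attendance or adherence rates, so every rate here is an assumption. Let a share a_C of controls attend. In the intervention arm the same kind of people attend, plus others drawn in, for a total share a_I. Habitual attenders are adherent with probability p_A = 0.80, those drawn in with p_M = 0.50. With no true effect on adherence:

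- control attenders: p_A = 80%
- intervention attenders: [a_C × p_A + (a_I − a_C) × p_M] / a_I
- difference = (1 − a_C / a_I) × (p_M − p_A)

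The fourth column adds a true effect of 15 points in both groups. The fifth keeps everyone randomised in the denominator and counts no record as failure; with no true effect that difference is (a_I − a_C) × p_M.

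| Attendance, control / intervention | Intervention attenders adherent | Attenders only, no true effect | Attenders only, true effect +15 | No record = failure, no true effect |
|---|---|---|---|---|
| 30% / 50% | (0.24 + 0.10) / 0.50 = 68.0% | −12.0 | +3.0 | +10 |
| 30% / 70% | (0.24 + 0.20) / 0.70 = 62.9% | −17.1 | −2.1 | +20 |
| 50% / 70% | (0.40 + 0.10) / 0.70 = 71.4% | −8.6 | +6.4 | +10 |
| 50% / 80% | (0.40 + 0.15) / 0.80 = 68.75% | −11.25 | +3.75 | +15 |

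With equal attendance (30% / 30%) the attender-only difference is 0. The sign follows p_M − p_A, so swapping the two adherence rates turns the third column into +8.6 to +17.1.

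**3. Precision among those observed, leaving bias aside.** Standard error = √(1.28 / n₁ + 1.28 / n₂), effect size 0.50:

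- 36 v 60: 55%
- 36 v 84: 60%
- 60 v 84: 74%
- 60 v 96: 77%

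Keeping 1.28 is slightly pessimistic, since fewer members per friend group would be observed. Treating all attenders as contributing to one biomarker is optimistic, since PrEP and ART biomarkers apply to different participants.

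**The case against.** The case on the other side has several good parts.

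- Biomarkers are one of several primary items, and the power calculation rests on a scale, so the survey-based comparison is not touched by this route. This stands and limits the scope.
- The table that defines the measures is not in the text, and the article does not say how biomarkers are coded. A yes/no variable for documented suppression would be complete for all participants and would fit the logistic option in Data analysis. Coding can be left to the SAP. The collection route cannot: the article fixes it, and an analysis plan cannot recover samples that were never taken.
- Controls are matched to facilities too, and Measures already records service use and the location of adherence. This helps a sensitivity analysis but does not make availability equal.
- The trial is a pilot for preliminary efficacy. This stands and lowers the severity.

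A reader might infer two stronger things. The first is that a real benefit would show up as harm. It can on chosen figures. Suppose 40% of each arm always attend, 70% of them suppressed, and a further 40% attend only because of LAFIYA, 40% of them suppressed. Attenders then give 70% v (0.28 + 0.16) / 0.80 = 55%, while all randomised give 28% v 44%. But the 16 points are 0.40 × 0.40, suppression newly recorded. They are a benefit only if those people would otherwise not have been suppressed, and the protocol says many seek care elsewhere.

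The second is that counting every absent record as failure restores the ITT comparison. The last column of the table shows that it can create +10 to +20 points with no true effect on adherence, in favour of the arm that attends more.

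**Conclusion.** The point holds for the biomarker component of the primary outcomes. Followed as written, the plan gives a biomarker comparison among self-selected attenders whose selection is likely to differ by arm, and the ITT statement does not describe it. That biomarkers come only from the participant's matched facility combines the Data collection and STEP 8 sections, and rests on no other route being stated.

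Direction and size are unknown. The −9 to −17 points and the 55–77% power show what assumed rates would do; they are not estimates for this trial. No figure in the Power section is wrong because of this, and the documents do not support the view that the whole primary analysis is invalid. Given the pilot purpose, it should be fixed, and it is not a bar to the trial.

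**What to change.** 1. Base the between-arm inference on HPART adherence on the survey measure scheduled for all YGBMSM at the designated sites. This agrees with the scale-based power calculation.
2. Report biomarker availability by arm, with attendance and consent shown separately. Label attender-only biomarker comparisons as descriptive and do not call them ITT.
3. If an all-randomised biomarker endpoint is also reported, use every randomised participant as the denominator. A subgroup by HIV status is unsafe: the eligibility criteria require no HIV test and the baseline described is a survey, so status may be learned after randomisation through testing that LAFIYA aims to increase. Name the endpoint documented engagement plus adherence or suppression, not adherence alone, and add a sensitivity analysis using self-reported care elsewhere.

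The change is one of wording, and the article states that recruitment has not begun. The price is that the main adherence comparison rests on self-report, still subject to survey attrition (10% assumed in the Power section), and that the biomarker results carry less inferential weight.

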### Measures.

#### Demography, HIV testing, and ISD descriptive variables.

We will assess important baseline characteristics for describing the sample, including age, income, gender, education, ethnicity, relationship status, religion, sexual orientation, sexual behavior, HIV knowledge, HIV testing, PrEP and ART readiness, and history. Experiences of ISDs, access, and utilization of health and social services, civic engagement, and neighborhood. **Primary outcomes:** At baseline, 3, 6, and 9 months, we will measure the preliminary efficacy of LAFIYA. We will measure knowledge of HIV and HPART; and willingness to adhere to HPART pre and post-intervention. HPART adherence characteristics (rates, time, mode, location) and biomarkers (Table 2). **Secondary outcomes:** For ISD reduction, we will measure internalized and interpersonal level ISD at baseline and post-intervention surveys among YGBMSM. We will measure HCF-level ISD to understand participant experiences at baseline and changes in HCW stigmatizing beliefs and practices (Table 2). **Implementation outcomes:** We will measure acceptability, appropriateness, and feasibility using expanded Proctors validated measures at pre-immediate and post-intervention surveys at all levels (Table 2)^103^.

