**Methodology:**

We will employ the ADAPTT-IT framework to adapt LAFIYA and evaluate its feasibility and effectiveness in addressing intersectional stigma and increasing HPART uptake among YGBMSM residing in Ghanaian slums. In aim 1, we will hold focus groups (n=5) and interviews (n=20) among YGBMSM and two FGDs among GBMSM-led organizations. At the HCF level, we will hold 6 FGDs and interviews (n=20) among nurses. In AIM 2, we will randomly assign 6 healthcare facilities (HCFs) to receive the LAFIYA (n=3) or wait-list control (n=3). Friend groups (cluster) of YGBMSM (N=240) will be assigned to receive LAFIYA (n=120) or a wait-list control (n=120). We will collect 3-, 6-, and 9-months post-intervention data among YGBMSM(n=240) and HCWs(n=300) to measure HPART adherence (primary outcomes), ISD reduction, HIV and status-neutral knowledge (secondary outcomes), and intervention acceptability, appropriateness, and feasibility (implementation outcomes).

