## Methods

### Study design overview.

We aim to adapt and determine the preliminary efficacy of a multilevel status-neutral intervention (LAFIYA) to address HPART adherence among YGBMSM in Ghana’s slums using the following **aims. 1)** Adapt a multilevel intervention to address ISD and HPART using status neutrality among YGBMSM. **2)** Test the preliminary efficacy of the intervention to address ISD and increase HPART adherence using CRT. We will use the ADAPTT-IT framework as a guide to adapt LAFIYA^75^. The framework offers eight steps: (1) Assessment, (2) Decisions, (3) Adaptation, (4) Production, (5) Topical experts, (6) Integration, (7) Training, and (8) Testing. We will use steps 1 to 7 to implement AIM1 and the results from AIM1 to inform AIM2. Aim 1 will produce the intervention manual. AIM 2 will constitute the CRT phase, where we will assess acceptance, feasibility, and appropriateness of the intervention (**implementation outcomes**), the preliminary efficacy of the intervention to reduce ISD (**secondary outcomes**), and increase HPART adherence (**primary outcomes**) among YGBMSM.

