#### HIV risk factors among YGBMSM.

We completed a 2022 formative study among **YGBMSM in Ghana’s slums** (Yale Fund for Lesbian and Gay Studies (FLAGS)). Qualitative interviews (n=15) show that YGBMSM have an increased HIV risk, e.g., inconsistent condom use and high transactional sex due to challenges with food insecurity. Some use sex work as their primary source of income. HIV knowledge was low, and HIV stigma was high. LAFIYA will address HIV/STD prevention knowledge gaps and reduce HIV ISD, especially age-group-specific HIV prevention needs of GBMSM youth.

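### HIV knowledge is a secondary outcome in the abstract but stands, with willingness to adhere, under the primary outcomes in the Measures section, so a gain in taught content could be reported as a primary-outcome effect

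*Protocol article*

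**What the plan says.** Four places in the protocol article assign outcomes to tiers or state what the trial is to show.

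- Abstract, *Methodology*: the follow-up surveys are "to measure HPART adherence (primary outcomes), ISD reduction, HIV and status-neutral knowledge (secondary outcomes". Knowledge is in the secondary tier, beside ISD.
- *Study design overview*: ISD reduction is secondary, and the primary aim is to "and increase HPART adherence (primary outcomes) among YGBMSM". Neither knowledge nor willingness is mentioned in any tier.
- *STEP 8 (Testing/Aim 2)*: the primary hypothesis "is that LAFIYA will increase adherence to HPART among YGBMSM participants". It covers adherence only.
- *Measures*, under the label for primary outcomes: "We will measure knowledge of HIV and HPART; and willingness to adhere to HPART pre and post-intervention". The next item under the same label is "HPART adherence characteristics (rates, time, mode, location) and biomarkers (Table 2". The secondary outcomes that follow are all about ISD, beginning "For ISD reduction, we will measure internalized and interpersonal level ISD at baseline and post-intervention surveys among YGBMSM" and going on to stigma at facility level. Knowledge is not among them.

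**The concern.** The primary tier settles which results the trial may present as its main findings. The Measures section places in that tier two survey constructs that the rest of the article either ranks lower or leaves out.

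Both are close to what the intervention delivers. *HIV risk factors among YGBMSM* states that "LAFIYA will address HIV/STD prevention knowledge gaps and reduce HIV ISD", and the participant component is a three-day retreat compared with a wait-list, so men will know whether they have attended when they answer the survey. The article's own background shows that attitude and behaviour can come apart. The *Introduction* reports that PrEP and self-testing are highly acceptable to GBMSM in Ghana while uptake stays low, and *PrEP uptake among YGBMSM* reports high acceptability once PrEP had been explained, alongside continuing difficulty with uptake and retention.

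At stake is what a mixed result would be called. Suppose knowledge rises and testing, PrEP and ART adherence do not. Under the abstract, that is a secondary finding beside a null primary result. Under the Measures section, it can be reported as an effect on a primary outcome. The findings are meant to shape a later efficacy trial, so the difference matters.

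**Working it through.** **Ranks side by side**

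| Construct | Abstract | Design overview | Primary hypothesis (Step 8) | Measures |
|---|---|---|---|---|
| HPART adherence | primary | primary | named | primary |
| HIV knowledge | secondary | not named | not named | primary |
| Willingness to adhere | not named | not named | not named | primary |
| ISD | secondary | secondary | not named | secondary |

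Adherence and ISD are ranked consistently. HIV knowledge has two incompatible ranks. Willingness is not ranked twice: it is primary in Measures and absent from the other tier lists. No text shown orders the measures within the primary list, and the *Data analysis* section applies its longitudinal model to the outcomes generally, without separating the tiers.

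**Reproducing the plan's power**

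Inputs from *Power*, YGBMSM: ICC 0.04, 8 men per friend group, 120 per arm, effect size 0.50, 5% significance (taken as two-sided, since the sidedness is not stated).

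- Design effect = 1 + (8 − 1) × 0.04 = 1.28, as stated.
- Effective number per arm = 120 / 1.28 = 93.75.
- Power = Φ(d × √(n/2) − 1.96) = Φ(0.5 × √46.875 − 1.96) = Φ(3.423 − 1.96) = Φ(1.463) = 92.8%. The noncentral t version gives 92.6%. The plan states 92.7%.
- With 10% attrition: 108 / 1.28 = 84.375, and Φ(0.5 × √42.19 − 1.96) = Φ(1.288) = 90.1%. The plan states 90%.

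The stated figures reproduce, so the sample-size arithmetic is not in question.

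**Illustration: a true knowledge gain with behaviour unchanged**

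The article gives no expected effect on knowledge, so the shift is an assumption and a range is needed. With 93.75 effective men per arm:

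| Assumed knowledge shift | d × √46.875 | less 1.96 | Chance of a significant knowledge result |
|---|---|---|---|
| 0.3 SD | 2.054 | 0.094 | 54% |
| 0.5 SD | 3.423 | 1.463 | 93% |
| 0.8 SD | 5.477 | 3.517 | over 99.9% |

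These are probabilities of detecting a real gain in knowledge. They show that a knowledge-only result under the primary label is a realistic outcome. They do not measure any inflation of type I error.

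**The case against.** The strongest reply is that the article's intent is plain. The primary hypothesis concerns adherence, the design overview agrees, and the abstract's conclusion lists adherence and knowledge as separate expectations. Measures also keeps adherence and biomarkers as primary. A knowledge-only gain would not satisfy the hypothesis, and nothing says that one significant primary measure makes the trial a success. All of this stands. A reader might infer that the trial would declare success on knowledge alone; the documents do not support that. They leave open only the narrower problem that such a gain could be reported as a primary-outcome effect.

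A reader might also set the 93% against a 5% error rate and conclude that false claims are inflated. That comparison is not valid: the first is power for a true knowledge effect, and the second would need a single adherence test, which the documents do not define. HPART combines testing, PrEP and ART, and the primary outcomes are plural throughout. Nor does the order of items in Measures amount to a ranking.

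Three smaller points are fair. The abstract speaks of status-neutral knowledge and Measures of HPART knowledge, so only HIV knowledge clearly overlaps. The abstract does not mention willingness, so it cannot be cited as making willingness secondary. Table 2 is not shown and may assign tiers, but that could not remove the conflict between the abstract and the Measures text.

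Finally, this is a pilot of preliminary efficacy, so less rests on a confirmatory claim. That lowers the stakes without making the two lists compatible.

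**Conclusion.** The concern holds as an inconsistency in the current text. HIV knowledge is secondary in the abstract and primary in Measures. Willingness is primary in Measures although it appears in no tier in the abstract or overview and lies outside the primary hypothesis. The consequence is confined to reporting: following Measures, a gain in taught content could be presented as a primary-outcome effect with adherence flat, even though the hypothesis would remain unmet.

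The only size attached is illustrative: about 54%, 93% or over 99.9% for an assumed true knowledge shift of 0.3, 0.5 or 0.8 SD. It rests on 120 men per arm, the plan's design effect of 1.28 and a two-sided 5% test. It assumes that the design effect given for the planning scale also applies to a knowledge score.

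The correction should be made before recruitment, which the trial status section says has not begun. It should run towards adherence, because the abstract, the overview and the hypothesis all point that way and Measures alone differs.

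**What to change.** In *Measures*:

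1. Keep only the HPART adherence characteristics and the PrEP/ART biomarkers under primary outcomes.
2. Move knowledge to secondary outcomes, beside ISD, to match the abstract. Describe the knowledge measure in the same terms in both places.
3. Move willingness to secondary outcomes as well. The reason is that the overview and the Step 8 hypothesis restrict the primary outcome to adherence; the abstract is silent on it.
4. Add one sentence stating that the primary hypothesis in Step 8 is judged on the adherence measures alone.

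Check that Table 2 carries the same tiers. The cost is a few sentences of text. The surveys and biomarkers are collected as planned, and the stated power of 92.7% (90% after attrition) is unaffected.
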